# Immunotherapy with FBTA05 (Bi20), a trifunctional bispecific anti-CD3 x anti-CD20 antibody and donor lymphocyte infusion (DLI) in relapsed or refractory B-cell lymphoma after allogeneic stem cell transplantation: study protocol of an investigator-driven, open-label, non-randomized, uncontrolled, dose-escalating Phase I/II-trial

**DOI:** 10.1186/1479-5876-11-160

**Published:** 2013-07-02

**Keywords:** B Cell Malignancies, Allogeneic Transplantation, Donor Lymphocyte Infusion, Immunotherapy, Trifunctional Bispecific Antibody (trAb)

## Abstract

**Background:**

Patients with B cell malignancies refractory to allogeneic stem cell transplantation (SCT) can be treated by subsequent immunotherapy with donor lymphocyte infusions (DLI). But unlike myeloid leukemia, B cell leukemia and lymphoma are less sensitive to allogeneic adoptive immunotherapy. Moreover, the beneficial graft-versus-lymphoma (GVL) effect may be associated with moderate to severe graft-versus-host disease (GVHD). Thus, novel therapeutic approaches augmenting the anti-tumor efficacy of DLI and dissociating the GVL effect from GVHD are needed. The anti-CD20 x anti-CD3 trifunctional bispecific antibody (trAb) FBTA05 may improve the targeting of tumor cells by redirecting immune allogeneic effector cells while reducing the risk of undesirable reactivity against normal host cells. Hence, FBTA05 may maximize GVL effects by simultaneously decreasing the incidence and severity of GVHD.

**Methods/Design:**

Based on this underlying treatment concept and on promising data taken from preclinical results and a small pilot study, an open-label, non-randomized, uncontrolled, dose-escalating phase I/II-study is conducted to evaluate safety and preliminary efficacy of the investigational antibody FBTA05 in combination with DLI for patients suffering from rituximab- and/or alemtuzumab-refractory, CD20-positive low- or high-grade lymphoma after allogeneic SCT. During the first trial phase with emphasis on dose escalation a maximum of 24 patients distributed into 4 cohorts will be enrolled. For the evaluation of preliminary efficacy data a maximum of 12 patients (6 patients with low-grade lymphoma and/or Chronic Lymphocytic Leukemia (CLL) / 6 patients with high-grade or aggressive lymphoma) will attend the second phase of this clinical trial.

**Discussion:**

Promising data (e.g. induction of cellular immunity; GVL predominance over GVHD; achievement of partial or complete responses; prolongation of time-to-progression) obtained from this phase I/II trial would represent the first milestone in the clinical evaluation of a novel immunotherapeutic concept for treatment-resistant low- and high-grade lymphoma and NHL patients in relapse.

**Trial registration:**

NCT01138579

## Background

### B cell malignancies

Approximately half of the patients with aggressive non-Hodgkin's lymphomas (NHL) and the majority of patients with low-grade lymphomas cannot be cured by conventional therapeutic treatment regimes. Intensive chemotherapy followed by stem cell support has improved survival of patients with chemotherapy sensitive lymphoma. The majority of these patients, however, will still relapse, even after high-dose therapy and subsequently have limited therapeutic options. Although allogeneic stem cell transplantation (allo-SCT) can induce long-term remission due to a graft versus lymphoma (GVL) reaction, this occurs predominantly in a highly selected population of indolent lymphoma patients. A GVL reaction is less pronounced in patients with aggressive lymphoma, resulting in a high relapse rate [1-7]. In patients not eligible for allogeneic stem cell transplantation, palliative treatment is restricted by resistance to chemotherapy and complications of infection. Therefore, new therapeutic strategies with improved anti-tumor efficacy need to be developed for such patients.

Immunotherapies with monoclonal antibodies (mABs) directed against the CD20 antigen have previously been shown to be highly effective. Rituximab (Rituxan; Genentech Inc, South San Francisco, CA, and Biogen IDEC Inc, Cambridge, MA), an immunoglobulin gamma (IgG) 1 chimeric mAb, induced overall response rates (ORR) up to 50% in patients with relapsed or refractory low-grade B cell lymphoma [8,9]. In first line-treatment, rituximab induces response rates up to 75% in patients with follicular or low-grade NHL [10]. But despite these encouraging results, there are still numerous patients who do not respond or finally relapse [11].

Efforts to further increase the therapeutic efficacy of antibodies resulted in the development of trAb FBTA05 which mediates effective tumor cell cytotoxicity even at low CD20 expression levels, and probably even more importantly, induces a lasting anti-tumor immunity [12-15].

### Compound review

FBTA05 is a heterologous antibody, composed of two potent heavy chain subclasses, a mouse IgG2a and a rat IgG2b chain, each with their respective light chains. It therefore possesses two specific and one functional binding site. FBTA05 binds with one binding arm to the CD3 antigen on T cells and with the second binding arm to the CD20 antigen, which is expressed exclusively on normal and malignant B cells, but not on hematological precursor cells or other human cell types. In addition, the third functional site within the hybrid Fc region binds to Fcγ receptor type I, IIa and III which are expressed by accessory cells (e.g., macrophages, dendritic cells, natural killer cells) of the immune system. In this “tri-cell complex”, an important “crosstalk” between T cells and accessory cells can occur, which includes co-stimulatory signals necessary for a physiological T cell activation cascade. The simultaneous activation of different immune cells at the tumor site results in efficient killing of tumor cells by several complementary mechanisms (e.g. release of cytokines, perforin-mediated lysis and phagocytosis). The antibody-mediated phagocytosis of tumor cells by accessory cells (macrophages and dendritic cells) is believed to result in the processing of tumor antigens and presentation on the surface of these cells. Since this can result in polyclonal humoral and cellular immune responses [13,14], a T cell response even against unknown, tumor-associated peptides may be induced.

The combined attack of various immune cells with different killing mechanisms induced by FBTA05 leads to a significant tumor cell elimination when compared to monospecific antibodies or conventional bispecific antibodies. In addition, the induction of a variety of effector mechanisms may result in a protective long-term anti-tumor immunity. The postulated mechanism of action of the trAb FBTA05 is shown in Figure 1.

**Figure 1 F1:**
[figure not shown]
**FBTA05 (anti-CD3 x anti-CD20 trAb) – mode of action.** In a MHC-independent manner polyclonal T cells are redirected to and activated at tumor cells by trAb-mediated recognition of CD3 and tumor-associated antigens (TAAs) such as CD20. At the same time or subsequently FcγR-positive accessory cells such as monocytes/macrophages, dendritic cells (DCs) or natural killer cells interact with the Fc part of trAbs. Through this cellular crosstalk all participating immune cells are strongly activated. Hence, T cells receive a second co-stimulatory signal, while accessory immune cells are stimulated via FcγR crosslinking which leads to the release of proinflammatory cytokines. Thus, tumor cells are effectively eliminated by a concerted attack of cytotoxic T cells and accessory immune cells using different killer mechanisms such as ADCC, phagocytosis, or perforin/granzyme-mediated lysis and apoptosis induction. Finally, T cell proliferation occurs as does phagocytosis of necrotic/apoptotic tumor particles which are then processed, and presented by stimulated professional antigen presenting cells (i.e. DCs), an important prerequisite for the induction of long-lasting vaccination-like effects against tumors. ADCC (antibody dependent cellular cytotoxicity); CMC (complement-mediated cytotoxicity); DC-CK1 (Dendritic cell cytokine 1); IL (interleukin); LFA (leukocyte function-associated antigen); TNF-α (Tumor necrosis factor α).

### Previous trials and clinical data

Prior to the start of the current phase I/II dose escalating study, FBTA05 was administered in a compassionate use setting to patients with recurrent and refractory B cell malignancies following allo-SCT, and within a phase I/II trial (IV-A05-LL-01, EudraCT No: 2006-006694-24) to patients with relapsed or refractory CLL in an autologous setting.

In compassionate use a limited number of advanced cancer patients were treated with FBTA05. These, included 4 patients with refractory Chronic Lymphocytic Leukemia (CLL), 4 patients with refractory high-grade non-Hodgkin Lymphoma (HG-NHL) and 1 patient with refractory Acute Lymphocytic Leukemia (ALL) [16]. The treatment comprised escalating doses of FBTA05 with a range of 10–2,000 μg per single infusion. The maximum cumulative dosage administered per patient ranged between 130–13,610 μg of FBTA05. The duration of treatment was between 5–76 days. Following FBTA05 treatment, patients received DLI. Due to the nature of the different indications, the number of peripheral B cells prior to the start of FBTA05 infusions showed a large variation. An anti-tumor response (decrease of leukemic cells and shrinking of lymph nodes) was observed in 3 of 4 CLL patients. In 1 case of HG-NHL, a halt of progression for almost 4 months was observed. The effect of FBTA05 in the other patients was not evaluable due to other concomitant treatment or disease (fungal infection). Relapse finally occurred in all patients. The main side effects were restricted to fever, chills, bone pain and transient increase in γ-glutamyl transpeptidase (γGT). Only one case of GVHD (grade 3) was observed after FBTA05 and DLI and this was in the ALL patient. In context of the administration of the highest cumulative dose of FBTA05 (6,240 μg), a transient granulocytopenia was detected in a HG-NHL patient. The cytokine profile was characterized by a transient increase of IL-6, IL-8 and IL-10. Human anti-mouse antibodies (HAMAs) were not detectable. According to the current experience with the anti HER2/neu directed trAb ertumaxomab there is a correlation between the formation of HAMA and human anti-rat antibodies (HARAs), so HARA development in these patients would seem to be unlikely [17].

Due to the changes in the development program of the sponsor (Fresenius Biotech GmbH) the phase I/II dose escalating study (IV-A05-LL-01, EudraCT No: 2006-006694-24) was prematurely terminated after treatment of 3 patients in the first cohort (maximum dose 100 μg FBTA05). Thus, no maximum tolerated dose (MTD) could be established and only limited data on drug safety are available. In general, the intravenous infusion of FBTA05 was assessed to be safe and well tolerated, even at higher antibody doses. However, due to the limited number of patients treated, to variable disease progression in individual patients and to a variety of different concomitant treatments used, this information needs to be interpreted with caution.

### Rationale for performing the study

Antibody based therapies (rituximab, alemtuzumab), especially in combination with chemotherapeutic regimes, offer some advantages in patients with CLL and B cell non-Hodgkin lymphoma (NHL). Nevertheless, most patients finally relapse. Especially patients with diffuse large B cell lymphoma (DLBCL) have a very poor prognosis in case of early relapse after chemotherapy combined with rituximab. Therefore, there is an urgent need to further develop alternative treatment options whereby the CD20 antigen represents a solid target for innovative therapeutic approaches: (i) it is expressed on most B-cell lymphomas, (ii) it is only expressed on B cells, but not precursor cells or human tissues and (iii) it is not shed or secreted upon antibody binding.

The trAb FBTA05 provides a novel and unique approach for the targeted treatment of CD20 expressing neoplasias. The potency of FBTA05 has been demonstrated by efficient in vitro killing of human B cell tumor cells, as well as cells derived from CLL patients expressing only low levels of CD20 [12]. FBTA05 in combination with DLI has already been administered to patients in compassionate use prior to the start of the scheduled phase I/II study and assessed to be feasible, safe and well tolerated even at high antibody and T cell doses. Most importantly, some anti-tumor responses were observed in 3 CLL and 1 NHL patient [16].

It is well established that DLI, given as a single treatment is effective in hematological relapse post-SCT, but it is suggested that concerted treatment with additional drugs may further improve treatment outcome [18,19]. Thus, the combination of DLI and the anti-CD20 x anti-CD3 trAb FBTA05 might be a promising treatment option for patients with B cell malignancies refractory to allo-SCT. Since both, the desired GVL and the unwanted detrimental GVHD responses are mediated by T lymphocytes present in DLI preparations, FBTA05 has the capacity to enhance these GVL effects as autologous and allogeneic T cells are targeted to tumor sites. At the same time as GVL of allogeneic T lymphocytes is strengthened by FBTA05 engagement the risks for GVHD development are reduced. Therefore, by adding FBTA05 to the established allogeneic DLI treatment regime patients may even benefit more from this combined therapeutic approach. Furthermore, FBTA05 should be given prior to DLI administration to allow the already bound anti-CD20 x anti-CD3 trAbs FBTA05 to attract incoming allogeneic T lymphocytes directly to the CD20-expressing tumor cells. In other words, this treatment setting may favor GVL enhancement by simultaneously minimizing GVHD risks. This application sequence may be also important to control cytokine release due the increased number of CD3^+^ T target cells of FBTA05 in the blood circulation after DLI infusion. The opposite application order for FBTA05 and DLI would not mediate this positive effect of pre-coating tumor cells with trAb FBTA05 in vivo for attracting incoming allogeneic T lymphocytes. Moreover, preclinical and first clinical data confirmed this beneficial sequence for FBTA05 and DLI application.

## Methods/design

The present trial is an investigator-initiated, open-label, multi-center, non-randomized, uncontrolled, dose-escalating phase I/II study designed to evaluate the safety and efficacy of the investigational trAb FBTA05 in combination with DLI for treatment of relapsed or refractory disease in CD20 positive CLL / low-grade NHL or high-grade NHL after allogeneic transplantation.

### Primary and secondary objectives

The primary objective is the determination of the MTD of FBTA05 in phase I (dose-escalation part). In phase II (efficacy part), it is the preliminary evaluation of efficacy of a treatment schedule with FBTA05 and DLI in patients with CD20 positive either CLL / low-grade NHL or high-grade NHL after allo-SCT. The secondary objectives are the evaluation of safety and pharmacodynamics of FBTA05 in combination with DLI, the induction of cellular immunity in terms of GVL or GVHD, and the determination of further efficacy data in terms of time to progression (TTP), duration of response and clinical benefit.

### Primary and secondary endpoints

The primary endpoint in Phase I is the incidence of dose limiting toxicities (DLTs), in phase II the objective response rate. The secondary endpoints are safety and efficacy. Regarding safety, the recommended dose of FBTA05 in combination with DLI for further efficacy studies will be determined. Furthermore, the incidence of adverse events (AEs), the presence of HAMAs after FBTA05 application, the need to discontinue FBTA05 infusion, vital functions, the physical examination findings, laboratory parameters, concomitant medication and as pharmacodynamic endpoints the serum levels of cytokines will be recorded.

In terms of efficacy the clinical benefit rate, the duration of response, the time to progression, the overall survival, the ECOG performance status, the tumor specific response, lymphocyte subsets, activation signs and memory status of T cells will be analysed.

### Study design

To evaluate differences in drug response to CLL/low grade NHL or high grade NHL, patients are enrolled into study cohorts according to their respective disease entity (either CLL / low-grade NHL or high-grade NHL). As shown in Figure 2, the complete treatment course consists of a drug induction part (safety part) with defined FBTA05 doses of 10 μg on day 0, 20 μg on day 3 and 50 μg on day 7, as well as a drug maintenance / escalation part (course I and II, see also Table 1). The final antibody infusion of each part is followed by a dose-escalated application of donor lymphocytes.

**Figure 2 F2:**
[figure not shown]
**Treatment schedule.** The FBTA05 treatment schedule consists of three parts: the drug induction part (safety part) and the dose maintenance / escalation parts (course I / II). Thereby the safety part is the same for each study patient, with FBTA05 applications of 10 μg on day 0, 20 μg on day 3 and 50 μg on day 7. FBTA05 dose adjustment for the subsequent treatment courses I and II, will be performed according to the respective cohort A-D (Table 1). Infusion of donor lymphocytes (DLI) will be dose-escalated (Table 3) and applied subsequent to the respective antibody infusions on day 7, day 35 and day 63 of the treatment schedule. The red arrows indicate the application of FBTA05, the green arrows the infusion of donor lymphocytes.

**Table 1 T1:** Dose escalation of FBTA05

**FBT05**	**Day**	**Cohort A**	**Cohort B**	**Cohort C**	**Cohort D**
**Safety part**	**d0**	10 μg	10 μg	10 μg	10 μg
	**d3**	20 μg	20 μg	20 μg	20 μg
	**d7**	50 μg	50 μg	100 μg	200 μg
**FBT05**	**Day**	**Cohort A**	**Cohort B**	**Cohort C**	**Cohort D**
**Course I**	**d14**	50 μg	50 μg	100 μg	200 μg
	**d21**	50 μg	50 μg	100 μg	200 μg
	**d28**	50 μg	50 μg	100 μg	200 μg
	**d35**	50 μg	100 μg	200 μg	300 μg
**Course II**	**d42**	50 μg	100 μg	200 μg	300 μg
	**d49**	50 μg	100 μg	200 μg	300 μg
	**d56**	50 μg	100 μg	200 μg	300 μg
	**d63**	50 μg	100 μg	200 μg	300 μg

FBTA05 (anti-CD3 x anti-CD20 trAb).

Each cohort includes at least 2 patients. In a strict sequential order, treatment and dose escalation (cohort A-D, Table 1) is performed independently for each disease entity (either CLL / low-grade NHL or high-grade NHL). Thus, treatment of any subsequent patient 2 or 3 at a certain dose level will be started only after the safety part treatment of the previous patient of the same disease entity is completed, and the External Safety Board (ESB), acting as a Dose Steering Board (DSB), agrees to the enrolment of the next patient. The same dose escalation procedure will be applied throughout the study for all Cohorts (A-D). If one dose-limiting toxicity is seen, a total of 3 patients of the same disease entity must be treated at that dose level. If two dose-limiting toxicities are seen at any dose level, treatment for this disease entity is terminated and the MTD will be established at the next lower dosing level. If 2 of 3 patients of the same disease entity in Cohort A show dose-limiting toxicities, the MTD has been reached and lower dose levels may have to be investigated.

After the phase I part of the study an interim analysis will be performed. Based on the outcome of this analysis the recommended dose (RD) for the phase II part will be proposed by the ESB and the investigators on the basis of the MTD and any other relevant safety issues. The recommended dose will not exceed the maximal dose foreseen in the protocol approved by the competent authority. The report of the interim analysis with the recommended dose will be presented to the ethics committee and competent authority. A maximum of 6 patients per disease entity will receive treatment during phase II. If the last Cohort at MTD level in phase I already included 2 or 3 patients for CLL/low grade NHL, respectively high-grade NHL, an additional 4 or 3 patients per disease entity will be enrolled in phase II.

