### Study treatment

FBTA05 is administered with a constant rate over 6 hours by intravenous (i.v.) infusion. To avoid infusion reactions typically occurring after i.v. antibody infusions, i.v. Paracetamol (1,000 mg) and i.v. Dimetinden (4 mg) are administered 30–60 minutes prior to the start of infusion. Three hours after the start of FBTA05 infusion, i.v. Paracetamol (500 – 1,000 mg) is repeated. Post-infusion, Paracetamol and Dimetinden are administered, as needed.

In phase I, each patient (cohort A – D) will undergo the same safety part and receive induction doses of FBTA05 on day 0 (10 μg), day 3 (20 μg) and day 7 (50 μg). During the maintenance part, FBTA05 applications are scheduled for course I on day 14 (± 1 day), 21 (± 1 day), 28 (± 1 day) and 35 (± 1 day), for course II on day 42 (± 1 day), 49(± 1 day), 56 (± 1 day) and 63 (± 1 day). Thereby dose escalation of FBTA05 will be performed according to the respective Cohort A – D (Table 1).

Donor lymphocyte infusion is scheduled in each cohort at the end of the safety part (day 7), as well as at the end of course I (day 35) and course II (day 63). The numbers of infused T cells are escalated according to the respective preparative regimen applied for allo-SCT as shown in Table 3. DLI will not be performed in case the of GVHD or active infection at the time of DLI, or in the rare cases that DLI is not available for technical reasons. In this case antibody application will be continued as scheduled without DLI.

**Table 3 T3:** Dose escalation of donor lymphocyte infusions (DLI)

**DLI**	**Haplo-identical SCT**	**HLA-identical SCT**
**d7**	5 ×10^5^ /kg CD3^+^ cells	1 ×10^6^ /kg CD3^+^ cells
**d35**	1 ×10^6^ /kg CD3^+^ cells	5 ×10^6^/kg CD3^+^ cells
**d63**	5 ×10^6^ /kg CD3^+^ cells	1 ×10^7^/kg CD3^+^ cells

*SCT* stem cell transplantation, *HLA* human leukocyte antigen.

In phase II the recommended dose will be applied according to the respective treatment schedule as determined in phase I.

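### The day-7 FBTA05 dose for Cohorts C and D is given as 50 μg in the text and Figure 2 caption but as 100 μg and 200 μg in Table 1

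*Protocol article*

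**What the plan says.** Three places give the safety part as 10, 20 and 50 μg.

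- Study design describes this part as having "defined FBTA05 doses of 10 μg on day 0, 20 μg on day 3 and 50 μg on day 7" and names no cohort.
- The Figure 2 caption gives the same three doses, says "Thereby the safety part is the same for each study patient", and assigns cohort-dependent dosing to courses I and II, which begin on day 14.
- Study treatment says that each phase I patient, in any of Cohorts A to D, "will undergo the same safety part and receive induction doses of FBTA05", again with 50 μg on day 7.

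Table 1 differs. Its day-7 row, labelled as part of the safety part, reads "50 μg 50 μg 100 μg 200 μg" for Cohorts A, B, C and D.

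Three other provisions depend on this entry:

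- The first DLI is given on day 7 in every cohort (Study treatment; Figure 2 caption).
- Under Study design, treatment of patient 2 or 3 at a dose level "will be started only after the safety part treatment of the previous patient of the same disease entity is completed" and the ESB has agreed.
- Study treatment states: "In phase II the recommended dose will be applied according to the respective treatment schedule as determined in phase I".

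**The concern.** In a dose-escalation trial the dose table defines the intervention. Here it conflicts with the text at the first infusion that combines antibody and donor lymphocytes. The Rationale section says that giving the antibody before the DLI may help control cytokine release, because DLI raises the number of circulating T cells the antibody can bind. By the article's own reasoning, the antibody dose on that day is safety-relevant.

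The two versions put the cohort-specific step-up on different days. Under Table 1 it comes on day 7, together with the first DLI. Under the text it comes on day 14, with no DLI that day.

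They also differ in what the gate on patient 2 or 3 has observed. Under the text, a Cohort C or D patient who completes the safety part has received exactly what a Cohort A patient receives. Under Table 1, that patient has had one infusion at the cohort's own dose.

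If the recommended dose is C or D, the open question passes into phase II, which repeats the phase I schedule.

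**Working it through.** The article prints no cumulative doses, so there is no stated total to reproduce. The inputs are the doses in Table 1 and the 50 μg day-7 dose in Study design, the Figure 2 caption and Study treatment.

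**Step 1. Where the versions differ.** Days 0 and 3 (10 and 20 μg) agree everywhere. Day 7 agrees for Cohorts A and B (50 μg). Courses I and II are given only in Table 1, so no conflict arises there. The conflict is one infusion of 11, in two of four cohorts.

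**Step 2. Cumulative dose by day 7.**

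- Text, all cohorts: 10 + 20 + 50 = 80 μg.
- Table 1, Cohort C: 10 + 20 + 100 = 130 μg, which is 50/80 = 62.5% more.
- Table 1, Cohort D: 10 + 20 + 200 = 230 μg, which is 150/80 = 187.5% more.

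**Step 3. Size of the steps.**

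| Step | Text, C | Text, D | Table 1, C | Table 1, D |
|---|---|---|---|---|
| Day 3 to 7 | 50/20 = 2.5 | 50/20 = 2.5 | 100/20 = 5 | 200/20 = 10 |
| Day 7 to 14 | 100/50 = 2 | 200/50 = 4 | 100/100 = 1 | 200/200 = 1 |

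**Step 4. Full-course totals over 11 infusions.**

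- Cohort C, Table 1: 130 + 3 × 100 + 5 × 200 = 1,430 μg. With 50 μg on day 7: 1,380 μg. Difference 50/1,380 = 3.6%.
- Cohort D, Table 1: 230 + 3 × 200 + 5 × 300 = 2,330 μg. With 50 μg on day 7: 2,180 μg. Difference 150/2,180 = 6.9%.
- Cohorts A and B: 480 and 730 μg in both versions.

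**Step 5. Patients governed by the disputed entry.** Assume that a disease entity escalates to D and that its recommended dose is C or D. Cohorts C and D each have 2 or 3 patients, and phase II adds 4 or 3 to bring the group at the recommended dose to 6. The count per entity is therefore 6 plus the size of the other of the two cohorts: 6 + 2 = 8 or 6 + 3 = 9. If both entities meet the assumption, 16 to 18 of the maximum 30 patients are affected. If neither entity reaches Cohort C, none are.

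**Step 6. Could it be a text-extraction fault?** Every row of Table 1 has four values. The day-7 row equals the rows for days 14 to 28, and the day-35 row equals those for days 42 to 63. The table is intact and regular, so a conversion error is an unlikely explanation.

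**The case against.** The best counter-argument is that the practical effect is small and that Table 1 may be right. Its pattern is consistent: the last infusion of each part already carries the dose of the next part. The three text statements are worded almost alike, so their agreement may be repetition rather than three independent confirmations. This point stands. The text outnumbers the table, but the article does not show which version was intended, and the remedy should not presume it.

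The limits on size also stand. One infusion is affected, full-course exposure hardly changes, and C and D receive 100 and 200 μg on day 14 in either version. Dose-limiting toxicities are counted by cohort either way. For Cohort B the gate on the next patient sees no cohort-specific dose in either version. Compassionate use gave 10 to 2,000 μg per infusion, although the article itself asks for caution with those data. The earlier phase I/II trial stopped after 3 patients at a maximum of 100 μg without establishing an MTD, so it gives little reassurance about 200 μg. ESB oversight and 24-hour hospital surveillance apply throughout.

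Finally, dosing follows the approved full protocol, which is not shown, so the discrepancy may exist only in the article. That is a reason to check the approved protocol first. It does not remove the contradiction, because the article states two doses rather than omitting one.

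**Conclusion.** The contradiction is real and has to be corrected. For Cohorts C and D the article gives two day-7 doses that differ 2-fold (100 against 50 μg) and 4-fold (200 against 50 μg), on the day of the first DLI and at the infusion that completes the gate for the next patient. Its importance lies in the timing and size of that step, not in total exposure. It changes no sample size, error rate or MTD rule. The count of 16 to 18 affected patients holds only if both entities escalate to D and the recommended dose is C or D. The contradiction itself needs no assumption.

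**What to change.** Check the approved protocol and state one day-7 schedule throughout, before any patient, or any further patient, is dosed in Cohort C or D. There are two ways to do it:

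1. Set the day-7 entries of Table 1 for Cohorts C and D to 50 μg, matching the text.
2. Amend Study design, the Figure 2 caption and Study treatment to say that the day-7 dose depends on the cohort, and have the ESB expressly confirm the 5-fold and 10-fold steps on the day of the first DLI.

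In either case, keep counting dose-limiting toxicities by cohort and report the day-7 dose actually infused alongside them. If the approved protocol already gives a single dose, correcting the article is enough.

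The cost is two table cells, or three sentences plus an ESB confirmation. No patients are added and the escalation rule does not change.

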### Safety management

An ESB, composed of three independent experienced clinical experts is responsible for the evaluation of the patients. Together with the investigators they decide, whether individual patients may continue the study, and whether or not dose escalation can be applied. The ESB is involved in the assessment and declaration of Serious Adverse Events (SAEs), Suspected Unexpected Serious Adverse Reactions (SUSARs) as well as the evaluation of dose-limiting toxicities (DLT). Moreover, based on the results of the interim analysis at the end of the phase I, the ESB together with the investigators will propose the recommended dose (RD) for phase II.

The condition for a DLT is fulfilled in the case of termination of treatment due to an adverse reaction. Thereby, the treatment schedule for a patient must be terminated if any toxicity grade ≥ 3, condition or adverse event (e.g. body temperature ≥ Grade 3 Common Toxicity Criteria (CTC) (40°C), systolic BP < 75 or > 210 mm Hg, pulse < 50 or > 150 bpm or a dyspnoea grade IV) does not normalize within 3 hours. Furthermore, treatment will be terminated in case of an anaphylactic reaction, including, but not limited to severe angioedema, severe bronchospasm, severe urticaria or anaphylactic shock which occurs during the infusion. An adverse reaction, including clinical conditions of CTC Grade ≥ 3 or clinically relevant laboratory abnormality of CTC Grade ≥ 3 which occurs after the infusion and does not resolve until the planned date of the next infusion will also be grounds for termination of treatment.

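### The one stated time gate (end of the day 0–7 safety part) comes four weeks before the highest dose of Cohorts B, C and D, and DLTs count by cohort label whichever infusion caused them

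*Protocol article*

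**What the plan says.** Under Study design, Cohorts A to D are run in order, separately for CLL/low-grade NHL and for high-grade NHL, with at least two patients each. The timing condition applies to "treatment of any subsequent patient 2 or 3 at a certain dose level", so its stated scope lies within a level. Under this condition, dosing of such a patient "will be started only after the safety part treatment of the previous patient of the same disease entity is completed". It further requires that the ESB "agrees to the enrolment of the next patient". Under Safety management, the ESB and the investigators together decide "whether or not dose escalation can be applied". Neither section says what exposure must have accrued before the next cohort opens.

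On doses, the Figure 2 caption states: "Thereby the safety part is the same for each study patient, with FBTA05 applications of 10 μg on day 0, 20 μg on day 3", with 50 μg on day 7. Study design and Study treatment agree. The caption adds: "FBTA05 dose adjustment for the subsequent treatment courses I and II, will be performed according to the respective cohort A-D". Table 1, however, puts 100 μg (C) and 200 μg (D) on day 7, inside the safety part.

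On stopping, one DLT expands the level to three patients. "If two dose-limiting toxicities are seen at any dose level", the entity is stopped and the MTD is placed one level down. Safety management defines a DLT as treatment termination for an adverse reaction. One ground for termination is a Grade 3 or higher reaction that arises after an infusion and is still unresolved when the next infusion is due. The definition does not tie a DLT to the infusion that caused it.

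**The concern.** The MTD is the primary objective of phase I and feeds the recommended phase II dose. Two features of the rule could distort it.

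- **Exposure.** The stated gate is met before any patient in B, C or D has received that cohort's highest dose. Nothing in the article prevents the next cohort from opening on that information alone.
- **Attribution.** Infusions are shared between cohorts, but a DLT counts against the cohort the patient is in. A toxicity of the common early doses can therefore fix the MTD as though the cohort's own step had caused it.

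**Working it through.** **1. The plan's own figures.** Four cohorts × 3 patients × 2 entities = 24, the stated phase I maximum. The total is 2 × (4×3 + 3) = 30 if the last cohort has three patients, or 2 × (3×3 + 2 + 4) = 30 if it has two. Both match the stated 30, so the escalation rule is read here as intended: two patients, a third after one DLT, stop at two.

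**2. Dose timing (Table 1 against the text).**

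| Cohort | Day 7, text | Day 7, Table 1 | First infusion differing from cohort below (text / Table 1) | Highest dose, first given | Infusions at highest dose by day 7 |
|---|---|---|---|---|---|
| A | 50 μg | 50 μg | – | 50 μg, day 7 | 1 |
| B | 50 μg | 50 μg | day 35 / day 35 | 100 μg, day 35 | 0 |
| C | 50 μg | 100 μg | day 14 / day 7 | 200 μg, day 35 | 0 |
| D | 50 μg | 200 μg | day 14 / day 7 | 300 μg, day 35 | 0 |

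A and B are identical on days 0, 3, 7, 14, 21 and 28: 6 of 11 infusions.

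**3. Gate against DLT criterion.** For the day-7 infusion, the next planned infusion is on day 14. A reaction after day 7 cannot be judged against the unresolved-reaction criterion until then, yet the gate is already met once day-7 treatment is complete.

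**4. Calendar, if no later condition applies.** Let one patient occupy 8 + r days: day 7 plus the 24-hour surveillance, then r days for ESB review and recruitment. The value of r is an assumption. With n patients per cohort, the next cohort can open n(8 + r) days after the current cohort's first patient starts. Nobody has received the day-35 dose if n(8 + r) < 35.

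- n = 2: r = 0 gives day 16, r = 9 gives day 34, r = 10 gives day 36. The condition holds for r = 0 to 9.
- n = 3: r = 3 gives day 33, r = 4 gives day 36. It holds for r = 0 to 3.

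Order of exposure with n = 2, counted from the first B patient's start: B first receives 100 μg on day 35. The first C patient receives it on day 16 + 2r + 7 = 23 + 2r (Table 1) or 16 + 2r + 14 = 30 + 2r (text).

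- Table 1: earlier than day 35 for r up to 5 (day 33).
- Text: earlier than day 35 for r up to 2 (day 34).

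The same expressions apply to 200 μg in D against C.

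**5. Attribution.** Suppose the infusions common to all cohorts cause a DLT in a proportion q of patients, independently, and the cohort-specific doses add nothing (both assumed). A level stops with probability p = q² + 2q²(1 − q) = 3q² − 2q³.

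- q = 0.10: p = 0.030 − 0.002 = 0.028. A passes but B, C or D stops: 0.972 − 0.972⁴ = 0.972 − 0.8926 = 0.079.
- q = 0.20: p = 0.120 − 0.016 = 0.104. The same event: 0.896 − 0.896⁴ = 0.8960 − 0.6445 = 0.2515.

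The plainest case needs no model. Two DLTs in B before day 35 place the MTD at A, on infusions that A's patients also receive.

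**The case against.** The strongest reply is that the quoted gate governs patients 2 and 3 within a level. A reader might infer that the protocol clears a cohort at day 7, but no section says so. Escalation is a separate ESB and investigator decision, and the requirement to run cohorts in strict sequence could be meant to imply more. A DLT window or evaluability rule may stand in the full protocol, which is not shown. This stands: early opening is permitted by silence and is not prescribed. What remains is that the only stated time condition does not fit Table 1, and no minimum exposure is attached to the ESB's decision.

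Other limits also stand. Cohort A receives its 50 μg inside the gate, so the exposure point does not reach it. Under Table 1, C and D do have a cohort-specific dose on day 7, though not their highest. Small r is a fast calendar for patients relapsing after allogeneic transplantation, and the change in order of exposure disappears at r = 6 (Table 1) or r = 3 (text). Late DLTs still count, and the recommended dose also rests on other safety issues reviewed at the interim analysis.

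On attribution, counting DLTs by assigned regimen is a coherent convention. Chance stopping happens under any rule with two or three patients, whatever the gate. Attribution by dose is not clean either, because the day-35 antibody step coincides with a higher DLI dose. But where B and A have received identical infusions, the convention says nothing about B's step.

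Two further inferences are not supported. The article does not say that a patient who leaves early counts as DLT-free. Nor is the overall stopping chance under step 5 (1 − 0.8926 = 10.7%, or 1 − 0.6445 = 35.5%) a measure of misattribution, since it includes stops in A, where the shared doses are A's own regimen.

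**Conclusion.** The point holds in this form. The stated gate precedes the first infusion at the highest dose of B, C and D by four weeks (day 7 against day 35), and precedes by one week the date at which one DLT criterion can be judged for the day-7 infusion. As written, C and D can open with nobody in the cohort below at its highest dose. D has no cohort above it, but its patients 2 and 3 can start before 300 μg has been given to anyone. How often this would happen depends on r, which the article does not give. ESB discretion may prevent it.

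The two-DLT rule, applied as stated, can name A as the MTD for toxicities that arose on A's own regimen. The size, about 8% or 25% per entity for a higher cohort stopping after A passes, rests on assumed shared-dose DLT rates of 10% or 20% and no added toxicity from the cohort doses.

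The day-7 conflict between the text and Table 1 is plain on the page and changes when C and D first depart from the cohort below.

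**What to change.** 1. Reconcile the day-7 dose in the text and Figure 2 caption with Table 1 for Cohorts C and D.
2. Reconcile the gate and the MTD rule with Table 1. The plan should state which exposure a patient must have had to count towards clearing a cohort, and how a DLT on an infusion shared with the lower cohort bears on the MTD.
3. List each DLT with the FBTA05 dose and any DLI received, and summarise DLTs on shared infusions over all patients.

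No dose, observation interval or clinical rule is proposed here; those are for the sponsor, the investigators and the ESB. The cost is protocol wording and extra columns in the DLT listing, with somewhat slower cohort opening and an occasional patient who does not count towards clearing a cohort.
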